In a recent review the effect of tDCS on fatigue in neurological disorders, 42 studies were identified. These studies included a total of 994 participants. Amongst these 42 studies, five of them, involving 290 subjects, examined the effect of tDCS in PSF. In 36 out of 42 (85.7%) of studies reported an improvement in fatigue scores in the tDCS group. Side effects of tDCS are usually mild (42). Hence tDCS proves to have a promising simple, low-cost, portable, non-invasive and risk-free procedure for reducing fatigue symptoms in alleviating PSF. The objective of this proposed project will be to examine the effect of tDCS on PSF. We hypothesize that active tDCS is more effective than sham tDCS.

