### Primary outcome measure

The MFIS will be administered before treatment (T0), after 10 treatment sessions (T1, 1 day after the fifth treatment day), and 1 week (T2), 2 weeks (T3) and 4 weeks (T4) thereafter (36), at the same time of day. The time window of administration will be adjusted to assess changes between time points (4 weeks for T0, 1 day for T1, 1 week for T2 and T3, and 2 weeks for T4). The participants and the research assistant who administers the MFIS will be blinded to the delivered treatment.

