### Sample size estimates

Statistical power was computed using Power Analysis & Sample Size 2005. We assumed that the standard deviation of the MFIS score at baseline will be 3.9 (60), that the sham stimulation will not cause any change in fatigue and that a decrease of at least 3.0 MFIS points will be clinically relevant (36). Hence, the effect size of tDCS will be (3.0/3.9 = 0.77). Given that such a large effect size is unusual in clinical contexts, we will instead use a more realistic effect size, i.e., 0.50. One pairwise comparison will be performed in the analysis of variance. A sample size of 63 per group (a total of 126 participants) will give rise to 80% power in identifying the main effect of tDCS (73). Thus, assuming a dropout rate of 20%, 156 (126/0.8) participants will be recruited.

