### Statistical analysis

We will perform a per-protocol analysis and an intention-to-treat analysis. Only participants who complete treatment will be included in the per-protocol analysis, whereas all of the participants who receive at least one tDCS session will be included in the intention-to treat-analysis. A last-observation-carried-forward approach will be adopted for the analysis of outcome data. The mean score of the FSS will be calculated. The sum of individual item scores will be computed for the MFIS and the total score and physical, cognitive and psychosocial subscores will be derived. Demographic characteristics will comprise age, sex, and scores on the Chinese version of the GDS, the Chinese version of the HADSA, the PASE, the BI, the PSQI, and the NIHSS, and the severity of PSF will be measured using the FSS and the MFIS. Chi-square tests (for categorical variables such as sex) and t-tests (for continuous variables such as age) will be used to compare baseline performance. The effects of tDCS upon completion of treatment (T1) will be studied by entering the participants’ scores on the MFIS (total score and subscores) into a mixed-model analysis of variance with baseline MFIS scores as covariates, and the tDCS intervention (T0, T1) and stimulation (active, sham) as between-participant factors. The trend of tDCS effects will be studied by entering the participants’ scores on the MFIS (total score and subscores) into a linear mixed model with the tDCS intervention (T0, T1, T2, T3 and T4) and stimulation (active, sham) as within-participant factors. Pairwise comparisons between baseline and individual post-measurement-day significant results will conducted using Bonferroni t-tests for related samples. Withdrawals will be analyzed by logistic regression. The level of significance will be 0.05.

The safety analysis will be descriptive and exploratory. Key safety measures will be based on the tDCS AEs questionnaire and include the overall incidence and intensity of AEs; the number of AEs leading to treatment discontinuation; skin reactions; and other AEs.

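### The only follow-up tests named are paired baseline-versus-visit t-tests, so statements about how long benefit lasts (T2–T4) would lean on comparisons that leave out the sham arm

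*Protocol article*

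**What the plan says.** The aim is comparative. The Introduction closes with "We hypothesize that active tDCS is more effective than sham tDCS", and the Sample size estimates section plans a two-group comparison: "A sample size of 63 per group (a total of 126 participants) will give rise to 80% power".

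The Statistical analysis section then sets out three layers for the MFIS.

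- **T1.** A mixed-model ANOVA with baseline MFIS as covariate and "the tDCS intervention (T0, T1) and stimulation (active, sham) as between-participant factors".
- **T0–T4.** A "linear mixed model with the tDCS intervention (T0, T1, T2, T3 and T4) and stimulation (active, sham) as within-participant factors", intended to show the trend of the effect.
- **Follow-up comparisons.** "Pairwise comparisons between baseline and individual post-measurement-day significant results will conducted using Bonferroni t-tests for related samples".

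The overall level is given by "The level of significance will be 0.05". The visits are fixed under Primary outcome measure: "after 10 treatment sessions (T1, 1 day after the fifth treatment day), and 1 week (T2), 2 weeks (T3) and 4 weeks (T4) thereafter". The same section varies the MFIS window by visit: "4 weeks for T0, 1 day for T1, 1 week for T2 and T3, and 2 weeks for T4".

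**The concern.** A t-test for related samples that sets a later visit against baseline uses only differences within participants. Run in each arm or in both arms pooled, it contains no active-versus-sham contrast. It keeps whatever change the two arms share, and the protocol gives three reasons to expect some.

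- **Selection.** Entry requires an FSS of 4.0 or more. In Table 1 the screening visit is the only pre-treatment occasion for the fatigue scales, so selection and baseline coincide. Regression to the mean follows for the FSS, and for the MFIS as far as the two scales correlate.
- **Sham response.** The sample size section assumes there is none. A paired test depends on that assumption; an arm contrast does not.
- **Recall window.** T0 covers 4 weeks, T1 covers 1 day, T2 and T3 cover 1 week and T4 covers 2 weeks. Every paired difference from T0 therefore also compares two different windows. An arm contrast removes any shift common to the arms.

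At stake is the account of how long benefit lasts. A visit that is significant against baseline in the active arm but not in the sham arm is easily read as efficacy, even when the arms do not differ.

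**Working it through.** **1. Which comparison was powered.** Inputs from Sample size estimates: effect size 0.50 SD, power 80%. Alpha is 0.05; two-sided is assumed because sidedness is not stated.

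n per group = 2(1.960 + 0.842)² / 0.50² = 62.8, rounded up to 63.

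The stated figure reproduces as a two-sample calculation, so the powered comparison is active against sham. A one-sided version gives 50 and does not fit.

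**2. What each planned analysis says about the arms.**

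| Analysis | Visits | Active-versus-sham information |
|---|---|---|
| Mixed-model ANOVA | T1 | Yes: stimulation is between participants, with baseline as covariate |
| Linear mixed model | T0–T4 | Stimulation is present but labelled within-participant; no stimulation-by-time term or visit contrast named |
| Paired t-tests | Each later visit against T0 | None |

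Each participant receives one type of stimulation, so stimulation cannot vary within a participant. For T2–T4 the only visit-specific comparisons named are the paired ones.

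**3. How often a one-arm result would mislead.** Assumptions:

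- The tests are run separately by arm and are not conditional on a model result.
- There is no true difference between arms.
- n = 63 per arm.
- Bonferroni is applied over four later visits: 0.05/4 = 0.0125, two-sided.
- Both arms share the same standardised mean change dz (mean change divided by SD of change).

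The documents give no value for dz, so a range is shown. The critical value is t = 2.573 on 62 degrees of freedom. The power p of one paired test comes from the noncentral t distribution with noncentrality dz√63. The arms are independent, so active-only significance has probability p(1−p), and significance in exactly one arm (either) has probability 2p(1−p).

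| Common dz | p | Active only | Either arm only |
|---|---|---|---|
| 0 | 0.0125 | 1.2% | 2.5% |
| 0.20 | 0.171 | 14% | 28% |
| 0.25 | 0.287 | 20% | 41% |
| 0.30 | 0.430 | 25% | 49% |
| 0.35 | 0.583 | 24% | 49% |
| 0.50 | 0.915 | 8% | 16% |
| 0.70 | 0.998 | 0.2% | 0.4% |

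The ceiling is 25% for active only (50% for either arm), reached when p = 0.5. The range 0.25–0.35 therefore lies around the worst case. Under the same null a valid between-arm test keeps its nominal level whatever the common change.

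**4. Effect of gating.** If the paired tests followed only a significant between-arm result at 0.05, simulation of 20,000 trials at each of dz 0.25, 0.30 and 0.35 puts one-arm-only significance at about 5% in either direction, and active-only at about 2.4%.

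**5. Power of arm contrasts.** With 63 per group and an effect of 0.50 SD, the standardised difference is 0.50/√(2/63) = 2.806. Baseline adjustment at an assumed correlation of 0.5 divides this by √(1 − 0.25), giving 3.240.

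- Single T1 contrast at 0.05: Φ(2.806 − 1.960) = 80% unadjusted; Φ(3.240 − 1.960) = 90% adjusted.
- One visit at 0.0125: Φ(2.806 − 2.498) = 62% unadjusted; Φ(3.240 − 2.498) = 77% adjusted. At an assumed correlation of 0.7 it is 92%.

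**The case against.** The strongest reply is that the hypothesis is tested elsewhere. T1 has its own baseline-adjusted ANOVA with stimulation between participants, the T0–T4 model also contains stimulation, and the paired tests are only follow-up. That stands for T1. A reader might infer from the follow-up sentence that the plan has no between-arm test at all, or that the primary comparison is invalid; the documents support neither. For T2–T4 the reply is weaker, because the trend model mislabels stimulation and names no term or contrast that would give an arm difference at a visit.

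A second reply is that the sentence does not say whether the tests run by arm or pooled. Its garbled reference to significant results may also mean they follow only a significant model result. This stands as well. If they are pooled, one-arm significance cannot arise, although the test still does not compare arms. If they are gated on an arm effect, the risk falls to the level shown above; a gate on the time effect would protect less. The text does not settle which applies.

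A third reply is that the misleading pattern is frequent only for a modest common change. That is correct. Under the protocol's own assumption of no sham change, and with no true arm difference, active-only significance is about 1% per visit. A reader might infer that one-arm significance will often occur, or take the 41–49% as the risk of a false efficacy reading. The documents give no common change to support the first, and the second figure counts sham-only results too.

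Finally, contrasts by visit are often left to a statistical analysis plan. Here, though, the article names a specific test, so the point corrects a stated choice and does not fill a gap.

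**Conclusion.** The point holds in limited form. The named follow-up tests do not compare active with sham, and this is true for any size of change and whether they are run by arm or pooled. The T1 comparison and the sample size are not affected. The weakness lies at T2–T4, where the plan names no usable arm contrast and the paired tests would carry the statements on duration.

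The numerical risk is conditional on ungated testing by arm and on the assumed common change. It rises to about one in four for active-only significance at a visit and is small at both ends of the range. Since it concerns follow-up inference and can be mended in wording, it is a should-fix.

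**What to change.** In the longitudinal MFIS model:

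- Declare stimulation a between-participant factor and visit the within-participant factor.
- Include the stimulation-by-visit term.
- Adjust for baseline MFIS. In the current text that covariate belongs only to the T1 ANOVA, while T0 is an outcome level in the trend model, so the model sentence needs rewriting along with the follow-up sentence.
- Keep the T1 active-minus-sham contrast as the main one.
- Report active-minus-sham differences with confidence intervals at T2, T3 and T4, with Bonferroni or Holm control.
- Report within-arm changes from baseline descriptively, without tests.

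The cost is a few sentences of analysis text. No extra data, visits or participants are needed. The T1 contrast keeps its planned 80% power, or about 90% with baseline adjustment at an assumed correlation of 0.5. Bonferroni over the three later visits (0.05/3 = 0.0167) is less strict than the 0.0125 used above, so the 62% to 92% shown there is a lower guide for T2–T4 if the effect is still 0.50 SD at those visits.

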#### Access to data

Only the Principal Investigator ([name]) will have access to the final dataset.

#### Discussion and summary

We will endeavor to obtain a homologous sample by obtaining a set of participants with a narrow range of ages, ethnicities, handedness and duration of PSF. Potential participants with other causes of fatigue, such as depression, psychiatric disorders, alcohol/substance abuse and neurological disorders, will be excluded. We will use two tDCS devices to achieve bilateral stimulation of the motor cortex with a relatively high current and long duration of stimulation. The MFIS will be used to measure the primary outcome (a change in PSF severity), as it is commonly used in clinical trials of interventions for fatigue. A variety of secondary outcomes will be assessed, such as mood, quality of life and functioning. A conservative estimate of effect size has been used to calculate an adequate sample size. On the other hand, exclusion of patients with aphasia will limit the generalizability of the study’s results to this subgroup of patients. This proposed project will provide proof-of-concept, i.e., will demonstrate the benefits of tDCS in the treatment of PSF, thereby stimulating further research to determine the optimal tDCS parameters to alleviate PSF.

## Ethics statement

The studies involving humans were approved by the Joint CUHK-NTEC CREC (CREC: ref 2020.550). (The Chinese University of Hong Kong (CUHK) and New Territories East Cluster (NTEC) Clinical Research Ethics Committee). The studies were conducted in accordance with the local legislation and institutional requirements. The participants provided their written informed consent to participate in this study.
